## Abstract

**Introduction:**

Nursing students are exposed to increased risks of developing foot and ankle disorders due to prolonged standing and walking positions during clinical settings. This can lead to high dropout rates from nursing degree, thus contributing to a future shortage in nursing professionals. This protocol aims to develop a study to understand the influence of prolonged standing and walking positions on nursing students' foot health, and specifically to study the relationship between the podiatric profile (regional force and pressure exerted on the foot) and related signs and symptoms.

**Methods and Analysis:**

A prospective observational cohort study will be conducted with 194 nursing students. Participants will be asked to walk through a baropodometric platform before and after a 5-month clinical training session. Assessment will focus on the change in podiatric profile, namely foot posture and foot function, at 5 months, and changes in foot health at 5 months. The study will start in January 2022 and it's expected to end by June 2022.

**Discussion:**

The study aims to perform an innovative assessment of nursing students' podiatric profile, which will allow for a comprehensive description of foot/ankle changes and their relationship with prolonged standing and walking contexts.

**Ethics and Dissemination:**

The study was approved by The Ethical Committee of the Health Sciences Research Unit: Nursing (UICISA: E), of the Nursing School of Coimbra (ESEnfC), with the approval code nr. P799_07_2021. The study was also recorded in ClinicalTrials.gov on the number NCT05197166. Findings will be used to publish articles in peer-review scientific journals and oral communications and posters at scientific meetings.

## Introduction

Nurses are one of the healthcare professionals most exposed to occupational health risks, mostly due to prolonged standing and walking contexts (1, 2). Evidence has suggested that prolonged standing is associated with the development of adverse health outcomes (3), particularly lower-limb disorders. One of the most common disorders concerns the ones in the foot/ankle region (4, 5).

Stolt et al. (6) state that prolonged standing is considered the second work-related factor hindering foot health, increasing the risk for the development of significant disorders, and affecting the quality of life. However, these disorders are a large and often unrecognized group of diseases (4, 6) having poor evidence based on the scarcity of related research. As so, the biomechanics of many foot disorders remain poorly understood (7), particularly the influence and relationship between biomechanical variables and external stressors, such as, prolonged standing or walking positions.

According to Bakker et al. (8), the increase in physical demands while in clinical settings is an important contributor to nursing students' late-dropout, thus contributing to the future professional shortage. Data from a recent prospective cohort study (9) shows that musculoskeletal complaints, including foot/ankle disorders, accounted for 39.9% of intention to leave nursing education and an actual dropout rate of 3.4% among nursing students. In fact, many authors state that the foot and ankle regions are the most commonly affected and reported locations for the development of disorders in nursing students (10–14).

In this sense, to effectively prevent future disorders, and for an adequate foot self-care promotion among nurses and nursing students, a suitable evaluation and description of the podiatric profile are necessary. Furthermore, a categorization of the most important foot/ankle variables that are affected by standing environments, as defined by Bernardes et al. (15), as potentially aggressive contexts in the nursing profession, often implying continuous static-bound positions (while standing) or continuous dynamic movements (with long built-up walking distances throughout the shift time), is deemed important for the development of preventive interventions.

An evaluation and assessment of foot and ankle dynamic variables, while in static or dynamic positions, can be performed by various means. One of the most reliable method to determine the podiatric profile and respective variables, namely plantar pressure, is baropodometry (16). It's usually used to analyze the pressure areas exerted by the body in both motion and static positions, providing a dynamic gait analysis, distribution of loads during walking, peak pressures, and contact time with the ground, and also detection of areas in risk on the foot. Many previous studies have used plantar pressure assessments to identify foot pathologies and risk factors (17), with important results, namely detecting altered regional loadings (18), significant differences in foot kinematics (19) and pronated foot function (20).

Therefore, this paper aims to describe a protocol for a prospective observational study on the influence of prolonged standing and walking positions on nursing students' foot health, and relationships between the podiatric profile (regional force and pressure exerted on the foot) and related signs and symptoms.

## Methods and Design

### Study Design and Setting

A prospective observational cohort study will be conducted between January 2022 and June 2022 in a Nursing public school in Portugal. Data collection will take place at the end of January and in the first days of February.

### Participants and Recruitment Process

The study will enroll nursing students from a Portuguese Nursing School, and which are exposed to standing environments during acute clinical settings (e.g., hospitals). The recruitment process will be developed according to the following inclusion criteria: (i) nursing students enrolled, at the moment of the study, in a Nursing degree; (ii) nursing students that, at the moment of the recruitment phase, are not enrolled in a clinical learning setting; and the following exclusion criteria: (i) diagnosed chronic systematic diseases (e.g., rheumatoid arthritis); (ii) diagnosed metabolic disorders; (iii) visible lower limb swelling; (iv) presence of contraindications for baropodometric-related measurements; (v) history of orthopedic neurological and/or musculoskeletal problems likely to affect gait; and (vi) students that, at the moment of the recruitment phase, are also committed to a professional working activity or involved in high competition sports, which might influence foot health (e.g., waitress, door-to-door delivery, among others).

Participants will first be addressed in a project presentation session, where informed consent will be provided for their analysis and signature. Subsequently, the days for data collection will be scheduled, taking into consideration the most convenient periods for students and the research team. In this sense, a convenience sample will be recruited, as students will voluntary show up to participate in the study. This sampling method was chosen, rather than randomization, due to time constraints regarding project schedule, and also the need to achieve a representative sample. As we are performing the study only in one Nursing School, due to researchers' availability and ethical approvals, randomization could include students that wouldn't be able or didn't want to be part of the research in progress. In this sense, the research team opted to include volunteers, also helping decrease potential loss to follow-up.

In the Nursing School involved in this study, clinical training has an average duration of 4 to 5 months for students in the third and fourth year of the Nursing degree. Thus, the study will depend on this timeframe for the respective follow-up period.

According to the defined criteria, all undergraduate nursing students at the third year will be recruited as participants. Each academic year, an average of 300 students are enrolled, and for a confidence interval of 95% and a margin of error of 5%, the sample size needed is 169 participants. Also, an a priori 0.05 significance level is defined and a response distribution of 50% is assumed. To prevent potential losses, we've added an additional 15% of the total sample size, thus aiming to recruit 194 students.

All data collection will take place inside the Nursing School, in specifically chosen places, previously tested for the study, and will be performed by two researchers, which will be different from those responsible to analyze data.

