### Exposures, Outcomes and Confounders

The exposure under study consists of a particular environment that poses particular biomechanical risks to the foot/ankle region. According to Bernardes et al. (15), standing environments include those of prolonged standing and prolonged walking, which can be defined as spending at least 5% of occupational time standing or walking (21).

The first primary outcome of interest is related to the change in podiatric profile at 5 months and will be evaluated at month 0 and month 5, being an objective and quantitative outcome. In this case, specific foot-related variables while walking will be recorded, illustrating the actual behavior of the foot during activity. The assessment of the podiatric profile follows the important premise that the medial longitudinal arch is one of the most important and highly variable structural characteristic of the human foot (22).

The relevant variables that describe this outcome are summarized in Table 1.

**Table 1 T1:** Specific podiatric profile variables.

**Category**	**Variables**	**Definition**
**Kinematic variables**	Forefoot width/spreading	Distance, in millimeters, between two straight lines perpendicular to the Chopart joint and tangential to most medial and most lateral points of the heads of first and fifth metatarsals, respectively.
	Foot angle at contact (sagittal plane)	Dorsiflexion angle at contact, in relation to the sagittal plane.
	Foot eversion	Or pronation, is an angular movement where the foot moves away from the medial plane.
	Foot adduction	Is the angular movement were the foot moves toward the medial plane.
	Foot external rotation	Rotation of the joint away from the midline, measured as an angle.
	Ankle inversion	Angular movement toward the medial plane.
	Medial longitudinal arch (MLA)	Located between the heel proximately and the medial three metatarsophalangeal joints anteriorly. Runs through metatarsals 1-3, sesamoid bones, cuneiform bones, navicular, talus, and calcaneus bones; the plantar aponeurosis, spring ligament, talocalcaneal ligament, and deltoid ligament; the flexor *hallucis longus*, flexor *digitorum longus, abductor hallucis*, flexor *digitorum brevis*, tibialis posterior.
	Ankle plantarflexion ROM in late stance	Refers to the angular distance of the movement around the ankle joint during the late stance of gait, characterized by a single limb support, and occurring before the swing period.

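### The 169 is justified by a survey margin for one proportion in a random sample of 300, which does not describe the precision or power of the primary analyses of within-student change in volunteers

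*Protocol article*

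**What the plan says.** The calculation is in the protocol article under Participants and Recruitment Process. Its inputs are the yearly enrolment ("Each academic year, an average of 300 students are enrolled"), the confidence level and margin ("for a confidence interval of 95% and a margin of error of 5%, the sample size needed is 169 participants"), and an assumed proportion ("a response distribution of 50% is assumed"). A significance level is also named ("an a priori 0.05 significance level is defined"). The recruitment target follows: "To prevent potential losses, we've added an additional 15% of the total sample size, thus aiming to recruit 194 students".

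The same section describes the sampling: "a convenience sample will be recruited, as students will voluntary show up to participate in the study". Among the reasons for preferring this to random selection, it lists the need for a representative sample.

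Under Exposures, Outcomes and Confounders, the first primary outcome is the "change in podiatric profile at 5 months and will be evaluated at month 0 and month 5, being an objective and quantitative outcome". The second is the change in self-assessed foot health over the same interval, with most observed disorders recorded as present or absent. Statistical Analysis plans significance tests of the before-after change at 0.05 and names an independent-samples t-test or Mann-Whitney test. It also says that the data of participants who are lost will be erased.

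**The concern.** The article states its sample size justification in full, so this is not a matter of detail left to another document. The justification belongs to a different kind of study: a cross-sectional survey that estimates one percentage from a random draw of a known list. Here the main question is whether measurements in newtons, kilopascals, millimetres and degrees, together with foot health, change within students over five months. A margin in percentage points on one proportion carries no information about that. It involves no power, no size of change and no SD of change, and the 0.05 significance level named beside it plays no separate part in the formula.

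The sampling assumption fails too. Both the margin and the finite-population correction rest on random selection from the 300, and the students select themselves.

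At stake is how the results will be read. A reader may credit the study with a precision of 5 points that its design does not provide, and cannot tell from the stated justification what change a non-significant result would leave open.

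**Working it through.** **Inputs.** From Participants and Recruitment Process: N = 300, 95% confidence (z = 1.96), margin e = 0.05, proportion p = 0.50, 15% addition.

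**1. Reproducing 169.**
- Size for an unlimited population: n0 = z²p(1−p)/e² = 1.96² × 0.25 / 0.05² = 384.16.
- Finite-population correction: n = n0 / (1 + (n0 − 1)/N) = 384.16 / (1 + 383.16/300) = 168.7, rounded up to **169**.
- Check of the margin at n = 169: 1.96 × √[(0.25/169) × (300 − 169)/(300 − 1)] = 4.99%.

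The stated figure is therefore exactly the one-proportion survey size with N = 300.

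**2. Reproducing 194.** 169 × 1.15 = 194.35, stated as **194**. The addition is done correctly.

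**3. Calculation against design.**

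| | What the formula assumes | What the article plans |
|---|---|---|
| Sample | Simple random sample from a closed list of 300 | Volunteers |
| Quantity | One proportion at one time | Within-student change, month 0 to month 5; the first primary outcome is quantitative |
| Aim | Width of a confidence interval | Significance tests at 0.05 |

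**4. What 169 could detect for a change (illustration).** The article gives no effect, SD of change or power, so no required size for a change analysis can be derived from it. What can be shown is the sensitivity at its own n. Assume one paired test at two-sided 0.05, no multiplicity adjustment, and d = mean change / SD of the differences. By the normal approximation, d = (z0.975 + z_power)/√n:
- 169 pairs, 80% power: (1.960 + 0.842)/13 = 0.216.
- 169 pairs, 90% power: (1.960 + 1.282)/13 = 0.249.
- 165 pairs, 80% power: 2.802/12.85 = 0.218.

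The noncentral t gives 0.217, 0.251 and 0.219. To two decimals that is 0.22 at 80% power and 0.25 at 90%.

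Complete pairs needed over an assumed range of d, from n = ((z0.975 + z_power)/d)²:

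| d | 80% power | 90% power |
|---|---|---|
| 0.15 | 349 | 467 |
| 0.20 | 197 | 263 |
| 0.25 | 126 | 169 |
| 0.30 | 88 | 117 |

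**5. Loss to follow-up.**
- Loss at which 169 remain out of 194: (194 − 169)/194 = 25/194 = 12.9%.
- If 15% were the loss rate: 194 × 0.85 = 164.9, about 4 below 169. Keeping 169 would then take 169/0.85 = 198.8, so 199, against 194 (5 more, 2.6%). On the article's own formula the margin at 165 would be 5.13%.

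**The case against.** **The margin is not wholly irrelevant.** Most observed foot disorders are recorded as present or absent, and a margin on a proportion bears on their prevalence. This stands for a prevalence at a single time point under random sampling. It does not extend to the change between month 0 and month 5, which is what both primary outcomes are.

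**The population of 300 fits the source.** The article recruits third-year students of one school, and its Discussion concedes that a single-school convenience sample limits external validity. This also stands: N = 300 is consistent with the stated source, and the article should not be charged with overlooking generalisability. What remains is that volunteers are not a random sample of the 300, and that volunteering is nonetheless offered as a route to representativeness.

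**The 15% allowance.** A reader might infer that 194 is the wrong inflation because 15% loss leaves fewer than 169. The article does not support that. It says only that 15% was added, gives no expected loss rate, and cites volunteering as a way to limit losses. The shortfall of about 4 appears only if 15% is taken to be the loss rate.

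**The 0.22 SD figure is not the planned analysis.** This is correct. Statistical Analysis names an independent-samples test, and the primary outcomes cover many variables (14 in Table 1 alone, plus foot posture, foot function and foot health). The figure holds only for a single paired comparison, and nothing in the article says whether 0.22 SD is a change worth detecting.

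**Conclusion.** The point holds as a mismatch between justification and design, not as an arithmetic error: 169 and 194 both follow from the stated inputs. The 5% margin belongs to a single proportion in a random sample of 300, and neither the volunteer sample nor the primary change analyses have that property.

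Two stronger readings are tempting and should not be drawn:

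- *That 169 is too few.* By the table above it is enough for a standardised change of 0.25 or more and falls short at 0.20 or less. The article gives nothing to decide which applies.
- *That the true margin is 7.5 points.* Dropping the finite-population correction gives 1.96 × √(0.25/169) = 7.5%, but this too assumes random sampling, now from an unlimited population. It is no more valid for these volunteers than 5%.

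The loss allowance is a minor, conditional matter. Even at 15% loss, the detectable change stays at about 0.22 SD. The reproduction of 169 and 194 rests only on figures in the article; the sensitivity figures rest on the assumptions listed in step 4 of the working.

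**What to change.** Keep the recruitment target of 194 and change the text around it:

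1. Drop the 5% margin as the justification, and do not put 7.5 points in its place.
2. State the sensitivity of the primary change analysis at the planned size, for example: *169 complete pairs give 80% power for a mean within-student change of about 0.22 SD of the differences (0.25 SD for 90%), for one paired test at two-sided 0.05, without multiplicity adjustment.*
3. Make Statistical Analysis agree with this. The statement is true only if the before-after comparison is analysed as paired, in place of the independent-samples test now named.
4. State the tolerated loss: 194 recruited keeps 169 pairs for losses up to 12.9%. If 15% is the loss expected, add that about 165 pairs would remain, still about 0.22 SD at 80% power.
5. Remove the statement that volunteer sampling was chosen to achieve a representative sample. The practical reasons given beside it can stay.

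The cost is rewording only, with no extra students. The price is that the stated precision becomes less favourable.

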### Exposures, Outcomes and Confounders

The exposure under study consists of a particular environment that poses particular biomechanical risks to the foot/ankle region. According to Bernardes et al. (15), standing environments include those of prolonged standing and prolonged walking, which can be defined as spending at least 5% of occupational time standing or walking (21).

The first primary outcome of interest is related to the change in podiatric profile at 5 months and will be evaluated at month 0 and month 5, being an objective and quantitative outcome. In this case, specific foot-related variables while walking will be recorded, illustrating the actual behavior of the foot during activity. The assessment of the podiatric profile follows the important premise that the medial longitudinal arch is one of the most important and highly variable structural characteristic of the human foot (22).

The relevant variables that describe this outcome are summarized in Table 1.

**Table 1 T1:** Specific podiatric profile variables.

**Category**	**Variables**	**Definition**
**Kinematic variables**	Forefoot width/spreading	Distance, in millimeters, between two straight lines perpendicular to the Chopart joint and tangential to most medial and most lateral points of the heads of first and fifth metatarsals, respectively.
	Foot angle at contact (sagittal plane)	Dorsiflexion angle at contact, in relation to the sagittal plane.
	Foot eversion	Or pronation, is an angular movement where the foot moves away from the medial plane.
	Foot adduction	Is the angular movement were the foot moves toward the medial plane.
	Foot external rotation	Rotation of the joint away from the midline, measured as an angle.
	Ankle inversion	Angular movement toward the medial plane.
	Medial longitudinal arch (MLA)	Located between the heel proximately and the medial three metatarsophalangeal joints anteriorly. Runs through metatarsals 1-3, sesamoid bones, cuneiform bones, navicular, talus, and calcaneus bones; the plantar aponeurosis, spring ligament, talocalcaneal ligament, and deltoid ligament; the flexor *hallucis longus*, flexor *digitorum longus, abductor hallucis*, flexor *digitorum brevis*, tibialis posterior.
	Ankle plantarflexion ROM in late stance	Refers to the angular distance of the movement around the ankle joint during the late stance of gait, characterized by a single limb support, and occurring before the swing period.
**Kinetic variables**	Initial peak vGRF	vGRF consists of the ground reaction force during walking, this is, the force exerted by the ground on the body (the sum of all forces that exist between a body and the supporting surface). Abnormal peaks or loading values can lead to overuse injuries. vGRF can be measured in different gait phases, like initial, breaking or propulsive stances. It's measured in Newtons (N).
	Breaking vGRF	
	Propulsive vGRF	
	Peak plantar pressure	Foot plantar pressure is described as the distribution of forces exerted in the field between the sole of the foot and the ground. It's measured in kilopascal (kPa).
	COP displacement (medio-lateral)	In biomechanics, COP is the specific point where the vGRF vector is applied. Its displacement consists of an oscillation, which might be identified in different axis of the body in relation to the ground.
	COP displacement (anterior-posterior)	

*ROM, range of motion; vGRF, vertical Ground Reaction Force; COP, center of pressure*.

This outcome includes foot posture and foot function assessments, which are relevant biomechanical measures, that can be extracted from the plantar pressure scans acquired previously.

Foot posture can be characterized using the modified arch index (MAI), which is calculated by the division of the foot length, minus the toes, in three equal portions, and also the division of pressure in the middle third by that of all three regions.

Foot function is characterized by the center of pressure excursion index (CPEI), which is a measure of foot function throughout the gait cycle, being defined as the distance between an imaginary line drawn from the first and last points of each foot's center of pressure (COP) trajectory and the COP as the distal third tertile of the foot. This value is usually normalized by foot width and multiplied by 100, to obtain a percentage excursion of the COP.

Following previous similar studies (7), CPEI and MAI's distribution are divided into quintiles. For the first, feet in the top and bottom quintile will be considered as having a supinated and pronated foot function, respectively, and for MAI, the top and bottom 20% will be considered *pes planus* and *pes cavus*, respectively.

Another variable of interest to characterize the podiatric profile is plantar loading characteristics. As there is no current consensus in the literature for the definition of adequate foot segments, this study will consider the templates of similar studies, which showed good reliability for plantar forces and pressures during barefoot walking in healthy adults (23). Namely, the regions to assess and compare are: lateral heel, medial heel, midfoot, 1st metatarsophalangeal joint (1MPJ), 2nd−5th metatarsophalangeal joint (2–5MPJ), hallux and the lesser toes.

The second primary outcome concerns the change in foot health at 5 months, a subjective evaluation by the participant, and is related to observed clinical parameters, signs and symptoms, namely skin, nails, foot structure, as well as presence and location of the pain. The Portuguese adaptation of the Self-Administered Foot Health Assessment Instrument (S-FHAI), a Likert-type instrument with four dimensions, will be used. It will be applied at month 0 and month 5. The majority of observed foot disorders will be recorded as either present or absent.

The study also includes the following secondary outcomes: (i) Foot Self-Care Knowledge, which is assessed between month 0 and month 5, through a four-dimensional questionnaire, where specific interventions for the promotion and prevention of foot and ankle disorders are evaluated; and (ii) Students' perceptions about the influence of foot health in their quality of life. It is evaluated through focus groups after exposure time (month 5).

Regarding potential effect modifiers and confounders, we expect that different nursing activities and ward typology (e.g., surgical units, intensive care) might produce diverse baropodometric patterns.

The primary and secondary outcomes, respective instruments for evaluation and timeframes for assessment are summarized in Table 2.

**Table 2 T2:** Primary and secondary outcomes assessment.

			**Assessment**	**Timeframe**		
				**Month 0**	**Month 3**	**Month 5**
**Primary Outcomes**	Change in Podiatric Profile at 5 months^*^	Kinematic variables	EMED® software	x		x
		Kenetic variables		x		x
		Foot posture	MAI analysis	x		x
		Foot function	CPEI analysis	x		x
	Change in Foot Health at 5 months	Skin health	Portuguese adaptation of the self-administered foot health assessment instrument [S-FHAI; (24)].	x		x
		Nail health		x		x
		Foot structure		x		x
		Foot pain		x		x
**Secondary Outcomes**	Foot self-care knowledge	Skin: structure, problems and care	Portuguese adaptation of the Nurses' Foot Care Knowledge Test (NFKT)		X	
		Nails: structure, problems and care			X	
		Foot structural deformities: identification and care			X	
		Disease specific foot problems: identification and care			X	
		Footwear: properties and suitability			x	
	Students' Perceptions	Perceptions on the influence of clinical settings and potential foot disorders in quality of life.	Focal groups			x

* *global evaluation through the Emed® platform; MAI, Modified Arch Index; CPEI, Center of Pressure Excursion Index*.

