### Statistical Analysis

The primary outcomes and the Foot Self-Care Knowledge (secondary outcome) will be analyzed using SPSS Statistics v25, namely with descriptive statistics (average; standard deviation; medians) with an *a priori* significance value of *p* < 0.05.

After verifying the type of distribution of the sample, using the Kolmogorov-Smirnov (KS) with Liliefors correction (suitable for samples with more than 30 subjects) (30), either the independent samples *t*-test (normal distribution) or the Mann-Whitney (test non-normal distribution) will be used to compare changes in outcomes before and after the exposure.

To relate variables of interest, namely podiatric profile variables and specific foot-health parameters, a Multiple Linear Regression will be computed and multivariate analysis of variance with repeated measures to detect significant interactions between variables.

To control confounding effects, we'll perform a stratification of variables, and evaluate the exposure-outcome association, also using Mantel-Haenszel (M-H) estimator for an adjusted result. Additionally, the Analysis of Covariance (ANCOVA) will be computed to assess the effect of certain factors on the outcome variables.

The secondary outcome, related to the students' perceptions, will be analyzed using ATLAS.ti v7 software, based on the content analysis as defined by Bardin (31). The different phases of analysis are: (i) pre-analysis; (ii) exploration of the material; and (iii) treatment of results, inference and interpretation. The categorical organization of the content will be performed *a posteriori*, through the following codification steps: (i) cutting—choice of units; (ii) enumeration—choice of counting rules; and (iii) classification and aggregation of chosen categories and units.

Potential missing data will be handled using marginal mean imputation, this is, computing the mean of the missing value, *X*, using the non-missing values and use it to impute missing values of *X*.

Regarding loss to follow-up, all data belonging to participants that choose to opt-out or are lost during the study, will be erased from storage, as explained in the informed consent document.

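### Two primary headings cover many co-equal variables tested at one 0.05 level, and the protocol contradicts itself on which of them are primary

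*Protocol article*

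**What the plan says.** **Primary outcomes.** Under Exposures, Outcomes and Confounders, the first primary outcome is change in podiatric profile at 5 months: "The relevant variables that describe this outcome are summarized in Table 1". Table 1 has 8 kinematic and 6 kinetic variables. The text then adds "This outcome includes foot posture and foot function assessments", measured by MAI and CPEI. It also names plantar loading as a further variable of interest: "the regions to assess and compare are: lateral heel, medial heel, midfoot" and four more. The second primary outcome is change in foot health, measured by the S-FHAI: "a Likert-type instrument with four dimensions, will be used". Table 2 places kinematic variables, kinetic variables, posture, function, skin, nails, structure and pain under the primary label, with no ranking.

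**Analysis.** Participants and Recruitment Process states that "an a priori 0.05 significance level is defined". Statistical Analysis repeats the 0.05 criterion and says "The primary outcomes and the Foot Self-Care Knowledge (secondary outcome) will be analyzed using SPSS Statistics v25". A t-test or a Mann-Whitney test "will be used to compare changes in outcomes before and after the exposure". The repeated-measures multivariate analysis of variance is assigned to interactions between variables.

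**Width of the primary set.** The Abstract (Methods and Analysis) describes the podiatric assessment as posture and function only. Study Layout, in justifying the mid-gait protocol, says that joint kinematic data lie outside the study's scope.

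**The concern.** A primary outcome should tell the reader in advance which result decides the question. Here each heading is a list, and nothing says which entry counts or how several entries combine. With a 0.05 test on each entry, a significant primary change can appear when nothing changed, and the result to lead with can be chosen after the data are seen.

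This matters more because the article describes one cohort and no comparison group, so the before/after tests carry the main inference. The Discussion expects the study to map changes caused by standing and walking and to lead to guidelines and preventive tools.

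The internal disagreement adds to the problem. Two analysts working from different sections could each defend a different primary set.

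**Working it through.** **The plan's own figures.** The article states no overall error rate. Its only design calculation is for one proportion. With a population of 300, 95% confidence, a 5% margin and a 50% response, n0 = 1.96² × 0.25 / 0.05² = 384.1. The finite population correction gives 384.1 / (1 + 383.1/300) = 168.7, so 169. Then 169 × 1.15 = 194.35, so 194. Both figures reproduce, but the calculation uses none of the outcome variables and so does not identify a lead variable.

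**Number of tests, by reading.**
- Abstract reading: MAI + CPEI + 4 S-FHAI dimensions = 6.
- Adding the 6 kinetic variables of Table 1: 6 + 6 = 12.
- Adding the 8 kinematic variables, as in Tables 1 and 2: 12 + 8 = 20.
- Adding the seven loading regions, which have no row in Table 2: 20 + 7 = 27.

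Both feet, and individual disorders recorded as present or absent, could raise any of these counts.

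**Chance of at least one false positive.** For k independent tests, each at a true 0.05 level, this is 1 − 0.95^k. The expected number of false positives is 0.05k.

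| k | 1 − 0.95^k | Expected false positives |
|---|---|---|
| 6 | 1 − 0.735 = 26% | 0.3 |
| 12 | 1 − 0.540 = 46% | 0.6 |
| 20 | 1 − 0.358 = 64% | 1.0 |
| 27 | 1 − 0.250 = 75% | 1.35 |

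**Correlation between variables.** The documents give no correlations, so these are assumptions. In a simulation of 20 equally correlated two-sided z-tests (200,000 runs), the chance was 54% at r = 0.3, 42% at 0.5, 29% at 0.7 and 16% at 0.9.

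**The named test.** The plan specifies an independent-samples test for two measurements on the same students. With within-person correlation ρ, the actual level of such a test is about 2 × [1 − Φ(1.96/√(1 − ρ))]. For assumed ρ of 0.3, 0.5 and 0.7 this is 0.019, 0.0056 and 0.0003. For 20 independent tests the overall chance is then about 32%, 11% and 0.7%. The percentages in the table therefore apply once a paired test is used.

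**The case against.** Five points can be made on the other side.

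- **The Abstract already points to lead measures.** It does narrow the podiatric outcome to posture and function, and Table 2 gives MAI and CPEI their own rows. This stands, and it is why the count starts at 6. It does not settle the matter, because Table 2 also lists kinematic and kinetic variables as primary.
- **The kinematic variables may never be tested.** Study Layout puts joint kinematics out of scope, and the main measured variables under Instruments are pressure, force, contact area and the centre-of-pressure line. This also stands: the eight cannot be counted as certain. Nor can all eight be discarded. Forefoot width, for one, is a distance and not a joint angle.
- **Separate testing is inferred.** The article never says outright that each variable gets its own test. Still, the only before/after tests named are univariate, no total score is defined for either outcome, and the multivariate analysis is not described as an overall test to be passed first.
- **An analysis plan may handle multiplicity, and much of the study is descriptive.** An adjustment method can properly be left to such a plan. The designation of primary outcomes is made in this article, and it is that designation which is unranked and inconsistent.
- **Independence is implausible, and the independent-samples test is conservative on paired data.** Both are correct, and both lower the figures. The second is a separate error and not a multiplicity safeguard: it would fall away when corrected.

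**Conclusion.** The point holds as a defect in how the primary outcomes are fixed. Many components share primary status and one 0.05 level, without hierarchy or composite, and the sections disagree on which components belong. Under independence and a true 0.05 level for each test, the chance of at least one false primary change is about 26%, 46% or 64%, depending on which section is followed. For the widest of these three sets it is about 42% or 29% at assumed correlations of 0.5 or 0.7. With a valid paired test, the chance exceeds 5% on every reading unless the measures are perfectly correlated.

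A reader might infer that there are at least 20 primary tests and that a false positive is more likely than not. The documents do not support that as a firm statement. The count of 20 needs all eight kinematic variables, which Study Layout puts in doubt. At 12 tests the figure is below one half even under independence. At 20 it drops below one half somewhere between correlations of 0.3 and 0.5. Component-wise testing is also the natural reading and not an explicit one.

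**What to change.** Reconcile the Abstract, Exposures, Outcomes and Confounders (with Tables 1 and 2) and Study Layout so that all give the same primary set.

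- Name the lead variable or variables for each primary outcome: for example change in MAI and/or CPEI, which the Abstract already emphasises, and change in one prespecified S-FHAI score.
- Test these with Holm at an overall 0.05. With two lead variables the smaller p-value is compared with 0.05/2 = 0.025 and, if it passes, the other with 0.05. With three, the steps are 0.05/3 = 0.017, 0.025 and 0.05. By comparison, two unadjusted independent tests would give 1 − 0.95² = 9.75%.
- Label all other Table 1, regional and domain variables secondary or exploratory, and report them with confidence intervals.
- State whether the kinematic variables will be collected and analysed.

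The lead measures are already planned at month 0 and month 5, so no extra data are needed. The cost is protocol wording, a slightly stricter threshold for the lead variables and fewer results that can be called primary.
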